## Abstract

**Background:**

Hospitalizations involving opioid use disorder (OUD) are increasing. Addiction consultation services (ACS) initiate medications for opioid use disorder (MOUD) in hospital settings and arrange post-hospital follow-up for ongoing MOUD care. Engagement in MOUD following hospital discharge is hampered by challenges in timely access to MOUD. This protocol describes an open-label randomized comparative effectiveness trial comparing ACS treatment as usual (TAU) to a single injection of a 28-day formulation extended-release buprenorphine (XR-BUP) on MOUD engagement 34-days following hospital discharge.

**Methods:**

Six U.S. hospitals with ACS capable of prescribing all MOUD (i.e., methadone, buprenorphine, and extended-release naltrexone) recruit and randomize hospitalized patients with OUD who have not been on MOUD in the fourteen days prior to hospitalization. TAU may consist of any MOUD other than XR-BUP. Participants randomized to XR-BUP may receive any MOUD throughout their hospital stay and receive a 28-day XR-BUP injection within 72-hours of anticipated hospital discharge. There is no intervention beyond hospital stay. Participants are followed 34-, 90-, and 180-days following hospital discharge. The primary outcome is engagement in any MOUD 34-days following hospital discharge, which we hypothesize will be greater in the XR-BUP group. Randomizing 342 participants (171 per arm) provides 90% power to detect difference in the primary outcome between groups with an odds ratio of 2.1. Safety, secondary, and exploratory outcomes include: adverse events, MOUD engagement on days 90 and 180, opioid positive urine drug tests, self-reported drug use, hospital readmissions and emergency department visits, use of non-opioid drugs, fatal and non-fatal opioid overdose, all-cause mortality, quality of life, and cost-effectiveness. Data are analyzed by intention-to-treat, with pre-planned per-protocol and other secondary analyses that examine gender as an effect modifier, differences between groups, and impact of missingness.

**Discussion:**

Engagement in MOUD care following hospitalization in individuals with OUD is low. This randomized comparative effectiveness trial can inform hospital ACS in medication selection to improve MOUD engagement 34-days following hospital discharge.

**Trial registration:**

NCT04345718.

## Background

Hospitalizations for opioid use disorder (OUD) have increased substantially over the past decade. Between 2016 and 2018, there were nearly 1 million hospitalizations related to opioid use disorder (OUD) annually in the United States [1]. While skin and soft tissue infections comprise a large segment of these hospitalizations, patients with OUD are also hospitalized for a wide spectrum of other conditions with major depression, acute kidney injury, and exacerbations of obstructive lung disease among the most common [1–4]. Few people are offered effective interventions for OUD during hospitalization, which may contribute to the 8% all-cause mortality rate observed in these patients in the year following hospital discharge [5, 6]. 

Medications for opioid use disorder (MOUD), especially methadone and buprenorphine, reduce all-cause mortality by more than 50%, reduce risk of infection with HIV and hepatitis C, and improve several social determinants of health [7–10]. Hospitalization is an opportune time to engage patients in MOUD [11, 12]. Failure to do so not only increases post-hospitalization morbidity and mortality but can complicate the course of care while the patient is still hospitalized and increase discharges before medically advised, hospital readmission, and incomplete courses of treatment (e.g., insufficient antibiosis) [13–16]. Increasingly, hospitals have adopted addiction medicine consultation services (ACS) to address MOUD initiation and other aspects of care for people who use drugs (PWUD) [17]. These services improve linkage to ongoing MOUD care post-hospitalization and reduce hospital readmission rates compared to patients not seen by ACS [18–20]. Timely linkage to ongoing MOUD following hospital discharge has been a challenge, however [21]. In one study, an average of 16 days was needed for patients to access ambulatory addiction services [22]. Patients discharged on sublingual buprenorphine often receive less than one-week of medication upon discharge, creating a risky gap where patients may face withdrawal, loss of tolerance, increased overdose risk, return to opioid use, and loss to follow-up. Rapid access to outpatient MOUD within one- or two-days following discharge decreases this risk but is challenging to achieve [23]. The advent of extended-release injectable buprenorphine (XR-BUP) in 7- and 28-day formulations may improve ongoing engagement in MOUD in community settings [24, 25] but little is known about its impact on facilitating transitions of care from hospital to community care.

This open-label randomized trial in hospitalized patients with OUD who have not been on MOUD in the 14 days prior to admission, tests the comparative effectiveness of a 28-day formulation of XR-BUP administered within 72 h of anticipated hospital discharge versus ACS treatment as usual (TAU, consisting of either methadone or sublingual buprenorphine) on MOUD treatment engagement 34-days following hospital discharge. We hypothesize that XR-BUP, which offers more time for successful linkage than TAU, will result in a greater proportion of patients engaged in MOUD 34-days post-hospitalization. This outcome is adapted from the Health Effectiveness Data and Information Set (HEDIS) Initiation and Engagement of Substance Use Disorder Treatment (IET) measure used by more than 90% of health plans and specified by the National Committee on Quality Assurance (NCQA) [26, 27]. The measure, while imperfect, allows evaluation of treatment engagement up to 34 days following hospital discharge and has been validated in studies that find associations between meeting the measure and improved patient outcomes [20, 28]. While HEDIS defines engagement as two or more alcohol or other drug services within 34 days of initiation of alcohol and other drug dependence treatment, here we modify the measure for OUD treatment, using treatment with a prescribed MOUD on day 34 as the primary outcome since exposure to MOUD in itself represents engagement. This adaptation has face validity in Medicaid data [29]. It should be noted that since this study was designed, HEDIS has developed a pharmacotherapy for opioid use disorder measure defined as the percentage of patients continuing MOUD for 180 days.

## Methods

### Study objectives and design

Funded by the NIH HEAL Initiative^®^ and conducted through a cooperative agreement in the National Institute on Drug Abuse (NIDA) National Drug Abuse Treatment Clinical Trials Network (CTN), CTN-0098A Exemplar Hospital Initiation Trial to Enhance Treatment Engagement (EXHIT ENTRE) is a multi-site open-label randomized comparative effectiveness trial of XR-BUP versus TAU for hospitalized patients with untreated OUD prior to hospital admission who are willing to initiate MOUD while hospitalized. The primary objective of this study compares MOUD engagement 34-days following hospital discharge in hospitalized patients randomized to ACS TAU versus a single injection of a 28-day formulation of XR-BUP prior to discharge. Secondary objectives compare safety, engagement in MOUD care at 90- and 180-days post discharge, drug use, hospital readmissions, and emergency room visits among participants randomized to TAU versus XR-BUP.

Advarra, a single independent commercial institutional review board (IRB), approved the study (Advarra Pro00047336), with all sites ceding to this single IRB. The study was also reviewed by an independent Protocol Review Board and subsequently a Data and Safety Monitoring Board (DSMB) appointed by the NIDA Center for the Clinical Trials Network (NIDA CCTN). The sponsor does not make decisions regarding publication of this or other study-related manuscripts (Fig. 1).

**Fig. 1 Fig1:**
[figure not shown]
Study Schema

### Study setting and site selection

Solicitation for hospitals to participate in the study are distributed through the NIDA CTN. To be eligible for participation, hospitals must have established ACS with the capacity to initiate all FDA-approved MOUD. Five hospitals with established ACS were recruited initially, with a sixth hospital added after study initiation to improve recruitment (for sites see https://clinicaltrials.gov/study/NCT04345718).

**Participating sites must**:

Have an existing ACS with experience initiating MOUD prior to hospital discharge.Have a buprenorphine waivered provider “champion” on the ACS who can commit the time required to oversee medical aspects of the study, perform medical assessments, confirm participant eligibility, order study medications, and evaluate and respond to adverse events that may occur during the study period (study protocol was developed prior to the 2022 X-waiver elimination).Have at least one other buprenorphine waivered provider able to perform medical aspects of this study.Have the staff required to recruit and retain participants.Have the staff required to collect research data (including biological specimens such as blood and urine).Have access to local laboratory services to process screening and monitoring specimens (e.g., blood and urine).Be able to manage (store, dispense, and dispose) study medication including having an XR-BUP Risk Evaluation and Mitigation Strategy (REMS) participating pharmacy, if required.

### Study participants

**Eligible participants must be**:

Hospitalized.At least 18 years of age.
Children are not included because addiction health services for them present different challenges and their access to methadone treatment is greatly restricted thus preventing adequate outcomes analysis.
Meet DSM-5 criteria for moderate or severe OUD.Willing to initiate MOUD, including buprenorphine.Able to speak English sufficiently to understand the study procedures and provide written informed consent to participate in the study.

**Participants are excluded from participation if**:

Anticipated hospital length of stay less than 24-hours as determined by the ACS.Affected by a serious medical, psychiatric, or substance use disorder that, in the opinion of the study physician, would make it unsafe to participate in the study or may prevent collection of study data. This may include:

Disabling terminal diagnosis for which discharge from hospital is not anticipated or for which hospice care is being sought.Severe alcohol or benzodiazepine use disorder that is anticipated to require complex medical detoxification which cannot be completed prior to randomization.

3.Taking a long-acting opioid other than buprenorphine (e.g., methadone, extended-release oxycodone, extended-release morphine) for each of the three days immediately preceding randomization.4.Liver enzyme tests (Aspartate Aminotransferase (AST), Alanine Aminotransferase (ALT)) more than 3 times upper limit of normal.5.Currently pregnant or breastfeeding.6.Known allergy to buprenorphine or components of FluidCrystal delivery system.7.Receipt of MOUD in the 14 days prior to hospitalization as maintenance treatment; however, patients may have received MOUD for withdrawal management during or prior to hospitalization at the time of enrollment.8.Are currently in jail, prison or other overnight facility as required by court of law and/or is considered a prisoner under local law or is under current terms of civil commitment or guardianship.9.Previously randomized as a participant in the study – individuals may only be enrolled and randomized once.

### Participant recruitment and consent

Recruitment procedures vary by site, but potential participants are drawn from each hospital’s pool of inpatients who have been identified by the ACS as having a possible OUD. Clinical or research staff approach these patients during their index admission to provide information about the study. Individuals providing verbal consent are prescreened under a HIPAA Waiver of Authorization by reviewing the electronic medical record to further assess inclusion/exclusion criteria. If a person meets initial eligibility criteria during the prescreening process, they give written informed consent prior to completing screening and baseline procedures. The informed consent process includes a quiz testing comprehension of study activities, alternatives, and potential risks and benefits, which may be repeated until answered correctly. Participants can opt to provide additional consent for blood collection and biobanking for potential future addiction- and MOUD- related genetic studies. Baseline data collection is completed prior to randomization.

### Randomization

Approximately 342 eligible participants are randomized in a 1:1 ratio to open-label XR-BUP or TAU (e.g., methadone, sublingual buprenorphine, extended-release naltrexone). The randomization process is performed by computer by a central data and statistics center (DSC). A permuted block randomization procedure with random block sizes is used. The DSC statistician generates the randomization schedule using blocks of varying sizes within strata (hospitals) to ensure lack of predictability along with relative equality of assignment across treatment groups. The randomization details such as block size are not conveyed to staff or participants. The DSC statistician reviews randomization data on a regular basis to ensure that the scheme is being implemented according to plan. A randomization slot, once used, is not re-allocated.

### Intervention

This study randomly assigns participants to ACS TAU or a single injection of 28-day formulation XR-BUP administered within 72 h of anticipated hospital discharge. This study is open-label and not blinded. There are no study interventions that extend beyond the index hospitalization or to facilitate care post-hospitalization or MOUD adherence beyond the standard care provided by the ACS. The ACS may initiate MOUD at any point during hospitalization. TAU may consist of any FDA-approved MOUD (other than XR-BUP) with the dose and amount of MOUD supplied upon hospital discharge determined by the ACS. For methadone, federal regulation prevents more than three days of dispensing outside of an opioid treatment program, whereas up to 30-days of buprenorphine may be provided upon hospital release. Although participants randomized to XR-BUP do not receive their XR-BUP injection until they are within 72-hours of anticipated hospital discharge, the ACS may offer other MOUD during their hospitalization per local standard of care, which reduces potential imbalance between arms in approaches to MOUD during recruitment and screening. The rationale for not providing XR-BUP until just prior to hospital discharge is to account for variable length of hospital admissions and prevent some participants receiving an injection early in a prolonged hospitalization where the effect of XR-BUP may wear off during hospitalization or shortly thereafter.

MOUD initiation strategies are determined by the ACS and doses titrated per their standard of care. Participants randomized to XR-BUP must tolerate at least one dose of sublingual buprenorphine prior to injection. As XR-BUP is available in three doses, participants can receive a dose commensurate with their current (if on a stable dose) or anticipated stable dose of sublingual buprenorphine. Available doses of XR-BUP (equivalent sublingual dose range) are: 64 mg (8–10 mg), 96 mg (12–16 mg), and 128 mg (18–24 mg). Because the lowest XR-BUP dose approximates 8 mg sublingually, participants are required to have an anticipated maintenance dose of at least 8 mg sublingually. Access to XR-BUP (CAM-2038, Braeburn, Inc.) is via an Investigational New Drug Application as it was not commercially available at time of study initiation, although it has since become available. The National Institute on Drug Abuse negotiated with Braeburn Inc. to procure donated XR-BUP for this study, the lead investigators were not part of this process.

Participant follow-up for outcome assessments occur 34-, 90-, and 180-days following discharge from the index hospitalization. Participants receive $50 for baseline assessment and enrollment and $50, $75, and $100, respectively for the three follow-up visits.

### Assessments

Study assessment and the schedule of study activities are presented in the Table. Where possible, assessments include validated tools that are used widely throughout other NIDA CTN studies. For example, the Substance Abuse and Addiction Collection of the PhenX Toolkit [30] is used at baseline to assess demographics (age, ethnicity, sex, race, educational attainment, employment status and marital status), BMI, Human Immunodeficiency Virus (HIV) Risk & Status, and substance use measures including age of onset, past 30-day quantity and frequency, and lifetime use for alcohol, tobacco and other substances.

While the Timeline Followback (TLFB) [31, 32] is used at each study visit to assess past month drug and alcohol use, we have adapted an additional TLFB that asks about daily use of MOUD in the specified timeframe for the 34, 90, and 180-day follow-up visits.

Tests for viral hepatitis (hepatitis B surface antigen and antibody, hepatitis C antibody with reflex PCR, if positive) and HIV with reflex viral load, if positive, are collected at baseline unless results from the 90-days prior to admission can be abstracted from the medical record.

Urine drug screens (UDS) are collected at screening/baseline and at each follow-up visit to assess secondary outcomes, unless the follow-up visit is fully remote. All urine specimens are collected using FDA-approved one-step temperature-controlled urine drug test cups testing for the presence of: opiates, oxycodone, barbiturates, benzodiazepines, cocaine, amphetamines, methamphetamines, marijuana, methadone, buprenorphine, phencyclidine (PCP), fentanyl, and ecstasy (MDMA). Results of UDS are not shared with participant clinical care givers.

Medical comorbidity is abstracted from the medical record problem list and/or discharge diagnoses as is the Comorbidity Severity Index (i.e., CMS-HCC Risk Adjustment [33]).

Pre- and post- XR-BUP injection evaluation for precipitated opioid withdrawal uses the Clinical Opioid Withdrawal Scale (COWS) [34] with a 5-point increase indicating precipitated withdrawal. An independent data and safety monitoring board (DSMB) convened by NIDA will have access to safety reports and will meet at least annually. The DSMB may receive aggregate data (blinded) as well as by randomization group (unblinded). The DSMB may recommend protocol modifications or even early study termination if either study arm has a clinically important excess of serious adverse events.

The majority of collected data are directly entered without personal identifiers into a secure electronic case report form (eCRF) system maintained by the DSC (Advantage eClinical). Data abstracted from the electronic health record or requiring a paper source CRF are transcribed from paper CRF to Advantage eClinical by study staff. Following study completion and publication of the primary outcome paper, as per NIH and HEAL Initiative policy, study data will be available through the NIDA data repository (Table 1).

**Table 1 Tab1:** Table of assessments

	Prescreening	Screening/ Baseline^a^	Randomization	TAU/XR-BUP Initiation	Date of Discharge	Follow-Up			As Needed
DAY					0	34	90	180	
**General measures**									
Prescreen Approach Log	X								
Verbal Consent	X								
Prescreening Form	X								
Written Informed Consent and Quiz		X							
Inclusion/Exclusion		X							
Locator Form		X				X	X		
PhenX [30] Core Tier 1 Forms		X							
Demographics Forms		X							
Treatment Satisfaction Survey								X	
Treatment Initiation and Non-Initiation				X					
Hospitalization MOUD					X				
Marijuana Use Assessment		X							
COVID-19 Impact Assessment		X				X	X	X	
Timeline Followback (TLFB) (Medications)						X	X	X	
Study Completion Form								X	
**Measure of Primary and Secondary Outcomes**									
Engagement in MOUD Post Hospital Discharge						X	X	X	
Hospitalization and ED Utilization (Related or Not to OUD)						X	X	X	
Urine Drug Screen		X				X	X	X	
Timeline Followback (TLFB) (Drug/Alcohol) [31, 32]		X				X	X	X	
**Clinical and safety assessments**									
Medical and Psychiatric History		X							
Physical Examination		X							
Injection Site Examination^b^				X		X			
Injection Site Reaction Form^c^				X		X			X
Hospitalization Diagnoses					X				
Medical Comorbidity [33]					X				
Vital Signs		X							
DSM-5 Checklist [35]		X							
Mental Health Follow-Up Assessment									X
Adverse Events, Including Serious Adverse Events			X^d^	X	X	X	X	X^e^	
Prior and Concomitant Medications		X	X	X	X				
Clinical Opioid Withdrawal Scale^b; f^ [34]				X					
**Clinical laboratory assessments**									
Pregnancy and Birth Control Assessment^g^		X							
Confirmed Pregnancy and Outcome									X
Liver Transaminases (AST and ALT)^h^		X							
Hepatitis B, Hepatitis C, HIV Antibody^h^		X	X						
Genetic Sampling^h^		X	X			X	X	X	
Family Origin		X							
**Exploratory measures**									
Healthcare and Services Utilization [36]						X	X	X	
Pain Assessment [37]		X				X	X	X	
Depression (PHQ-9) [38]		X				X	X	X	
Post-Traumatic Stress Disorder (PC-PTSD-5) [39]		X				X	X	X	
Quality of Life (WHOQOL-BREF) [40]		X						X	
Non-Fatal Opioid Overdose		X				X	X	X	
Fatal Opioid Overdose (collected on SAE form)			X^d^	X	X	X	X	X	
Addiction Severity Index-Lite (ASI-Lite) Drug and Alcohol Use [41]		X						X	
Post-Hospitalization Medical Appointment Follow-Up						X	X		
Antibiotic Adherence for OUD-Related Infections^i^						X	X		
Hospital Length of Stay					X	X	X	X	
Subsequent XR-BUP Injections (XR-BUP group only)						X	X	X	
Receipt of Other MOUD						X	X	X	
**Administrative forms**									
Protocol Deviations									X
Missed Visit and Visit Documentation Form		X		X		X	X	X	

Notes: ^a^Can be completed at different time points; ^b^For XR-BUP only; ^c^Completed only if reaction noted upon injection site examination; ^d^AEs/SAEs collected only after the participant is randomized; ^e^At 180-days, only SAEs are collected; ^f^COWS is assessed twice (before and two-hours after XR-BUP initiation) for each participant randomized to XR-BUP group only; ^g^Completed a second time before treatment initiation if there are more than 7 days between screening/baseline and treatment initiation; ^h^Collected only once during these visits and not at each indicated time point; ^i^Completed only by participants discharged from the hospital on antibiotics for drug-related skin and soft-tissue infections

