**Exploratory outcomes include**:

Proportion of participants with positive urine drug test for illicit drugs 34-, and 90-, and 180-days following hospital discharge.Proportion of participants with self-reported non-prescribed drug use 34-, and 90-, and 180-days following hospital discharge.Change in ASI-Lite measures from baseline to 180 days.Proportion of participants with self-reported medical follow-up at the 34- and 90-day visits.Proportion of participants adherent to antibiotic for OUD-related infections (e.g., endocarditis or skin-soft tissue infections) (when applicable).Self-reported alcohol use 34-, and 90-, and 180-days following hospital discharge.Hospital length of stay (for both the index hospitalization and readmissions).Self-reported 180-day hospital readmission rates.Self-reported 180-day ED visit rates.All-cause mortality rates at 30-, 90- and 180-days following hospital discharge.Comparative cost-effectiveness of XR-BUP and other MOUD.Non-fatal opioid overdose rates (discharge to 34-day visit and since last study visit at the 90- and 180-day visits).Fatal opioid overdose rates up to the 180-day visit.Satisfaction with MOUD treatment 180 days following hospital discharge.Self-reported 34- and 90-day hospital readmission rates related to OUD.Self-reported 34- and 90-day ED visits related to OUD.Quality of life.Receipt of subsequent XR-BUP injections (among the XR-BUP group only).Receipt of other MOUD treatments during follow-up (e.g., XR-BUP in the control group, methadone or SL-BUP in the XR-BUP group).

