### Outcomes analyses

The primary analysis compares the two groups (TAU and XR-BUP) for the primary outcome (engagement in MOUD care on the 34th day following hospital discharge) using the Cochran-Mantel-Haenszel test stratified by hospital under the principle of intention-to-treat (ITT), i.e., participants are analyzed in the group to which they were randomized irrespective of whether they received their assigned treatment. An additional analysis may be performed using a per-protocol analysis population (i.e., according to the actual treatment received).

Supplementary analyses of the primary outcome will be performed as follows: (a) consider gender as an effect modifier, (b) add adjusters for possible differences between groups, and (c) adjust for missing outcome data. Logistic regression is used for (a) and (b) whereas analyses adjusting for missing outcome data will use inverse probability weighting (IPW).

Analyses of secondary outcomes, broadly, will have a form similar to analysis of the primary outcome, or outcomes measured at multiple time-points (e.g., engagement in OUD care at 34-, 90-, and 180-days) will use a mixed-effect analysis with a person-specific random effect to capture correlation of a person’s multiple time-points. The particular form of analysis, e.g., logistic regression vs. normal-errors regression, will depend on the outcome, and outcomes on continuous or effectively continuous scales may be transformed before analysis (e.g., by taking the logarithm) to allow use of analyses that assume normally distributed errors.

Analytic approaches for exploratory outcomes are similar to those described for the primary and secondary outcomes. In addition, we will explore moderators and mediators of MOUD engagement and other outcomes such as hospital length of stay and antibiotic completion rates (where appropriate). Potential moderators and mediators include hospital length of stay, post-hospital discharge medical follow-up, quality of life, depression, post-traumatic stress syndrome, pain, and treatment satisfaction.

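### The antibiotic-adherence outcome names endocarditis, but note i of Table 1 limits its form to skin and soft-tissue infections

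*Protocol article*

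**What the plan says.** Three parts of the protocol article bear on this point.

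- **Outcomes, exploratory list.** The outcome is worded "Proportion of participants adherent to antibiotic for OUD-related infections (e.g., endocarditis or skin-soft tissue infections) (when applicable". The population is OUD-related infections, and endocarditis is one of two examples.
- **Table 1, exploratory measures, with note i.** The row "Antibiotic Adherence for OUD-Related Infections" is marked at the 34-day and 90-day visits and carries note i, which says who completes it: "Completed only by participants discharged from the hospital on antibiotics for drug-related skin and soft-tissue infections".
- **Outcomes analyses.** Moderators and mediators are to be explored for MOUD engagement and for "other outcomes such as hospital length of stay and antibiotic completion rates (where appropriate", with that last qualifier attached.

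**The concern.** The outcome definition and the collection rule describe different groups. The definition takes in endocarditis by name and, through its wording as a list of examples, other OUD-related infections. The rule admits one infection type and uses the word only.

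At stake is the meaning of one exploratory result. If the rule is what sites apply, the reported proportion would rest on skin and soft-tissue infections alone while its label promises more. The same variable feeds the exploratory moderator and mediator work. It also has some link to the trial's rationale: the Background lists insufficient antibiotic treatment among the consequences of not engaging patients in MOUD while they are hospitalized. Adherence that was not asked about at a day-34 or day-90 visit is hard to recover later.

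**Working it through.** No arithmetic applies. The article gives no figure for this outcome, and the point does not depend on alpha, power, rates or sample size. The check sets the texts side by side and looks for another data source.

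**Step 1. Who belongs to the outcome?** The exploratory list requires an OUD-related infection treated with an antibiotic. Endocarditis qualifies, because the sentence names it. The applicability qualifier at the end excuses participants with no such infection or no antibiotic. It cannot remove an infection named in the same sentence.

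**Step 2. Who completes the form?** Note i requires discharge on antibiotics for a drug-related skin or soft-tissue infection.

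**Step 3. Compare.**

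| Participant discharged on antibiotics for | In the outcome as defined? | Completes the form under note i? |
|---|---|---|
| Skin or soft-tissue infection | Yes | Yes |
| Endocarditis | Yes, named | No |
| Another OUD-related infection | Yes, since the infections named are examples | No |

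Only the first row has data. The other two have none if note i is followed.

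**Step 4. Is there another source?** The row "Prior and Concomitant Medications" in Table 1 runs from screening/baseline to the date of discharge and has no follow-up visit, so it cannot show adherence after discharge. The rows for medical appointment follow-up and for healthcare and services utilization are marked after discharge, but nothing in the article describes them as collecting antibiotic adherence. No other row does so.

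**Step 5. How many participants are affected?** The article does not give the share discharged on antibiotics or the mix of infections among them. The number cannot be estimated, and no bound more useful than the size of the trial can be drawn from the text.

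**The case against.** The strongest reply is that a footnote in a journal table is not the operating instruction. The Trial progress section says the protocol is in its fifth version, and neither that document nor the form is shown. The row title matches the outcome's wording, and only the note is narrower. Loose wording in a condensed note is as consistent with the article as a real gap in collection. This stands as a limit: the contradiction in the text is certain, the loss of data is not. It does not remove the point, because if the form is broader, the published note is wrong and needs correcting.

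Four stronger readings are tempting, and the article does not support them.

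- *The outcome cannot be computed at all.* A proportion adherent among participants with skin and soft-tissue infections can be computed. What fails is coverage of the population named.
- *Endocarditis is excluded silently.* Note i prints the restriction openly in the same article. The risk lies in a later result carrying the wider label.
- *About a quarter of the forms could still be corrected in July 2024.* With more than 265 of 342 recruited by then, at most 342 − 265 = 77 participants, or 77/342 = 22.5%, were still to be recruited. That is an upper bound on people not yet recruited, not a count of forms. Some participants already recruited may still have had visits ahead, and the form applies only to those discharged on antibiotics.
- *A planned analysis is compromised.* The moderator and mediator work is exploratory and is to be done where appropriate.

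**Conclusion.** The point holds as an inconsistency between the outcome definition and the rule for collecting its only described data source. As written, the two cannot both be followed for a participant discharged on antibiotics for endocarditis. If sites follow note i, adherence is available for the skin and soft-tissue subset only.

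The size is unknown, for want of any infection breakdown. The consequence is minor: this is one item in a long exploratory list, and the primary outcome, the sample size and the secondary outcomes do not depend on it. The conclusion about data loss rests on two assumptions that the article cannot settle: that the form and site instructions match note i, and that no source outside Table 1 records adherence after discharge.

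**What to change.** 1. Check which rule the adherence form and the sites actually follow.
2. Reconcile the two texts. Either widen note i to all OUD-related infections covered by the outcome, for the remaining visits and with a memo to sites, or restrict the exploratory outcome to skin and soft-tissue infections.
3. If collection so far was limited to skin and soft-tissue infections, report that one consistently defined population as the outcome for all participants, and show any wider data separately. A label that changes with enrolment date would give one outcome two populations.
4. State how many participants with other OUD-related infections have no adherence data. Table 1 schedules hospitalization diagnoses at discharge, which may allow this count.

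The cost is small: an edited note and a memo, with an existing form completed by some additional participants, or else a narrower outcome label. How many additional participants is not known. Treatment, randomization and the primary analysis do not change.
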